#### 7.4.1.5 Dermatological toxicity

The cumulative exposure of trial subjects to oral VEGFR tyrosine kinase inhibitors is associated with the dose dependent development of palmar plantar erythrodysesthesia (PPE) (Porta et al. 2007; Rosenbaum et al. 2008). Patients with PPE develop a painful blistering condition of the acral surfaces that is associated with focal areas of desquamation and callus formation. Xerosis (dryness) and erythema are often prominent features within the surrounding skin. The most commonly involved surfaces are those that are particularly subject to the forces of friction and pressure (palms, digits and soles of feet). In the most severe cases of PPE patients may require breaks in treatment and sometimes dose reductions.

General measures for managing PPE associated with oral VEGFR tyrosine kinase inhibitors (Schwandt A et al. 2009):

- Patients should be advised to make use of the following: cotton socks, shoes with extra support and gel insoles
- Topical emollient creams and lotions should be used to minimise dryness, pruritus and discomfort
- The use of oral anti-histamines can also be considered for the symptomatic management of pruritus
- The use of urea containing creams can be considered for the management of areas affected by hyperkeratosis

See Appendix 1 for details of recommended skin care products.

#### **7.4.1.6 Oral toxicity**

Mucositis may also occur as a schedule limiting toxicity in patients receiving cediranib.

General supportive measures to prevent/ minimise oral toxicity include the following:

- The gentle brushing of teeth and the use of non-alcohol based mouthwashes and toothpastes
- Symptomatic relief from cheilitis and mucositis may be provided by the use of lip balms and lignocaine containing mouth washes

See Appendix 2 for details of recommended oral care products

#### **7.4.1.7 Reversible posterior leukoencephalopathy syndrome**

Reversible posterior leukoencephalopathy syndrome (RPLS) is a rare syndrome affecting vascular endothelial cells in the brain that may lead to capillary leak and oedema, and was first described in 1996 (Hinchey et al. 1996). It has been associated with a number of conditions, including renal failure, hypertension, fluid retention, and the use of cytotoxic or immunosuppressive drugs. It has also been reported rarely in association with the use of VEGF inhibitors including bevacizumab and sunitinib. Cases of Magnetic Resonance Imaging (MRI)-documented RPLS have rarely been reported in patients receiving cediranib in clinical studies.

The syndrome can present in a variety of non-specific ways, including headache, seizures, lethargy, confusion, blindness and other visual and neurological disturbances. Hypertension may be present, but is not necessary for the diagnosis of RPLS. MRI is the most sensitive imaging modality to detect RPLS and is recommended in suspected cases to confirm the diagnosis. RPLS is reversible upon removal of any possible precipitating factors and control of hypertension.

Active management of hypertension according to the hypertension management guidelines in this section may be expected to reduce the incidence of RPLS. However, if any case of RPLS occurs that is confirmed by imaging (CT or MRI), cediranib should be immediately discontinued in addition to any other measures to alleviate symptoms and control blood pressure.

#### 7.4.1.8 Fatigue

Fatigue experienced by patients taking cediranib and/or gefitinib may be rapid in onset. During appointments patients should be specifically interrogated about fatigue, and estimated fatigue levels (according to CTC) should be recorded.

Patients should seek medical advice early if Grade 2 fatigue develops (moderate fatigue causing difficulty performing some activities of daily living).

#### Fatigue management

- In case of clinically significant fatigue in the investigators assessment, the patient may consider short treatment breaks (cediranib and gefitinib) of 2-3 days (max. 14 days allowed (21 days in consultation with the CI)). Care should be taken to ensure that the patients' nutritional status is optimised.
- Patients should be encouraged to drink plenty of fluids (1.5L/day- sips).
- Consideration should also be given to other causes e.g. depression, insomnia, thyroid function (see [section 7.4.1.2](#)), diarrhoea/dehydration, anaemia, drug use e.g. CNS depressants (antiepileptics) and anxiolytics or adrenal function.
- Patients should be encouraged to manage fatigue by alternating periods of rest with frequent light exercise, which may improve the symptoms in some cases.
- Patients should restart treatment when symptoms have improved.

## 7.4.2 Management of toxicity attributable to gefitinib

Dose interruptions should be used as the first approach to managing toxicity and dose reduction may be considered.

The events for which de-escalation of the gefitinib dose is recommended include:

- CTCAE grade 3 or higher toxicities of duration >3 days that are considered to be related to study treatment that are not responding to maximal supportive care within 48 hours, at the discretion of the investigator.

With the EXCEPTION of

- Rash ([section 7.4.2.1](#))
- Interstitial lung disease ([section 7.4.2.2](#))
- Diarrhoea ([section 7.4.3](#))

the following management plan should be followed for management of toxicity attributable to gefitinib:

Dose interruptions should be used as the first approach to managing toxicity. For CTC Grade 3 or more, dosing with gefitinib should be interrupted. Gefitinib dosing may be withheld for up to 14 days (or 21 days in consultation with the CI) for management of toxicity. If a longer interruption is required due to unresolved toxicity, gefitinib should be discontinued.

- If the symptoms promptly resolve to grade 1 or below with supportive care, consideration should be given to continuing the same dose of gefitinib along with appropriate continuing supportive care
- If the symptoms of the toxicity are considered related to gefitinib and do not resolve to grade 1 or below with maximum supportive care and following a dose interruption of up to 14 days (or 21 days in consultation with the CI), the next dose level of gefitinib below that being dosed should be instituted
- If the symptoms do not resolve and it is considered medically appropriate, investigators may choose to permanently discontinue gefitinib

For patients who have multiple low-grade adverse events short dose interruptions (ie, 2- 5 days) of the gefitinib tablets may help. Treatment can be restarted on resolution at the same dose

One dose reduction for the gefitinib treatment will be permitted during the study. No re-escalation of dose is permitted.

A maximum of a 14-day (21-day in consultation with the CI) delay in dosing for gefitinib is permitted. If a longer interruption is required due to unresolved toxicity, gefitinib should be discontinued. In addition, there are certain circumstances in which study medication should be permanently discontinued (see [section 13.1](#)).

#### 7.4.2.1 Skin toxicity

Skin rash is a commonly reported outcome of treatment with gefitinib (Herbst et al. 2003; Wacker et al. 2007). Typically the rash comprises an acneiform dermatitis but also includes xerosis (dry skin), hyperpigmentation, telangiectasia, nail and hair changes. Gefitinib should be interrupted or discontinued in patients that develop severe bullous, blistering or exfoliating conditions. It is recommended that patients use sunscreen and limit sun exposure while receiving gefitinib as sunlight can exacerbate any skin reactions that may occur. See Appendix 1 for a list of recommended skin care products.

**Table 8. Suggested dose adjustments for rash**

| Adverse Event Grade | Dose modification                                       | Management Guideline                                                                                                                                 |
|---------------------|---------------------------------------------------------|------------------------------------------------------------------------------------------------------------------------------------------------------|
| Grade A             | None                                                    | The following agents have been used to treat rash with varying results:
Alcohol-free emollient cream
Chlorphenamine
Topical corticosteroids |
| Grade B             | None                                                    |                                                                                                                                                      |
| Grade C             | Dose reduction (optional *).                            |                                                                                                                                                      |
| Grade D             | Dose reduction as for Grade C or discontinue (optional) | Topical drying agents are not recommended                                                                                                            |

\*Dose reductions for rash are not required and should only be considered if the rash is causing distress or discomfort to the patient.

#### Scale for describing gefitinib induced acneiform eruption

##### Grade

- A = erythema
- B = erythema with papules
- C = erythema with papules and pustules
- D = erythema with papules and confluent pustules

### **7.4.2.2 Interstitial Lung Disease**

The emerging safety profile of the gefitinib, in non-small cell lung cancer patients, suggests an overall treatment related incidence of Interstitial Lung Disease (ILD) of 1% (Cohen et al. 2003). Almost a third of the cases of ILD have been associated with fatal outcomes. The reported incidence of gefitinib associated ILD has been around 2% in the post-marketing experience in Japan, around 0.3% in approximately 23,000 patients treated with gefitinib in a US expanded access program and about 1% in studies utilising gefitinib in the first-line treatment of NSCLC (with similar rates of ILD in both treatment and placebo groups). In the Iressa Pan Asia (IPASS) study in NSCLC, 2.6% of the gefitinib arm suffered ILD compared to 1.4% of the comparator arm (carboplatin/paclitaxel).

Patients with concurrent idiopathic pulmonary fibrosis whose condition worsens while receiving gefitinib have been observed to have an increased mortality compared to those without concurrent idiopathic pulmonary fibrosis (Naito et al. 2008).

Patients typically present with acute dyspnoea that progresses relatively rapidly and invariably requires inpatient admission. In some instances patients develop associated symptoms of cough and low-grade fever.

Chest radiographs are found to be normal in 10% of patients with ILD and therefore there should be a low threshold for the further investigation of the following:

- Patients with symptoms of progressive breathlessness, exertion (dyspnoea) +/- a persistent non-productive cough.
- Patients with an abnormal chest radiograph
- Patients who have or develop a restrictive ventilatory pattern of lung function abnormalities

Treatment with gefitinib should be ceased in all patients with a suspected diagnosis of ILD. High resolution computed tomography (HRCT) scanning is suggested as the most appropriate investigation to follow routine chest radiography. Providing that the respective patient is sufficiently stable then formal pulmonary function testing (including spirometry and gas transfer measurements) should be performed. High-dose dexamethasone therapy can be initiated at the discretion of the treating physician (Camus et al. 2004; Seto et al. 2006).

### 7.4.3 Diarrhoea

Both cediranib and gefitinib are associated with diarrhoea and therefore action should be taken to manage diarrhoea as soon as symptoms develop.

The recommendations for diarrhoea management in this study are based on guidelines from the American Society of Clinical Oncology. The guidelines suggest the aggressive management of 'treatment induced' diarrhoea to ensure that complications are avoided and that further treatments can be administered without delays (Benson et al. 2004).

**Table 9. Assessment of diarrhoea according to CTCAE version 4.03**

| CTCAE v4.03
Grade | Patient without stoma                                                                      | Patient with stoma                                                            |
|----------------------|--------------------------------------------------------------------------------------------|-------------------------------------------------------------------------------|
| 1                    | Increase of <4 stools per day over baseline                                                | mild increase in ostomy output compared to baseline                           |
| 2                    | Increase of 4 - 6 stools per day over baseline                                             | Moderate increase in ostomy output compared to baseline                       |
| 3                    | Increase of $\geq 7$ stools per day over baseline; incontinence; hospitalization indicated | severe increase in ostomy output compared to baseline; limiting self care ADL |
| 4                    | Life-threatening consequences; urgent intervention indicated                               | Life-threatening consequences; urgent intervention indicated                  |
| 5                    | Death                                                                                      | Death                                                                         |

#### 7.4.3.1 Initial management of diarrhoea

- Patients should be made aware that they are likely to experience diarrhoea
- Patients should be given loperamide to take home with them
- If diarrhoea occurs patients should immediately start loperamide after the first episode (4mg initially then 2mg every loose stool) and continue to take it until they have been free from diarrhoea for at least 12 hrs (up to a maximum of 16mg/day)
- Patients should be encouraged to drink plenty of fluids. Electrolyte replacements (e.g dioralyte) are recommended.

Patients should seek advice early, from their physician or study nurse, if

- Grade 1 or 2 diarrhoea persists for over 24hrs despite treatment with loperamide
- Grade 3 diarrhoea develops

- Any grade of diarrhoea associated with vomiting, marked abdominal distension or inability to take oral fluids develops

#### **7.4.3.2 Management of persistent (>24h) or uncontrolled severe diarrhoea despite loperamide**

- Patients should be advised to stop the cediranib and gefitinib study tablets and care should be taken to prevent dehydration.
- Following evaluation, consider ciprofloxacin for 7 days particularly if the patient has a fever or is neutropenic (although ciprofloxacin is a potential CYP450 inhibitor (see Appendix 3), in this instance it will be given whilst the patient is not on study medication).
- Consider infectious causes and aetiologies such as Clostridium difficile/viral gastroenteritis.

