#### **7.4.3.4 Dose modifications for cediranib and gefitinib for diarrhoea**

Diarrhoea which is Grade 1 in severity can be managed symptomatically without necessitating interruption of the trial drugs. Diarrhoea which is  $\geq$  Grade 2 in severity will require the trial drugs to be interrupted and restarted when the diarrhoea resolves to Grade 1 or less, with or without a dose reduction as shown in Table 10. Dose reductions of cediranib and gefitinib will be made depending on the current dose of each agent according to the flowchart in Figure 1, giving preference to the reduction of cediranib prior to gefitinib.

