**Table 10. Guidelines for dose modification for diarrhoea (for grading see table 9)**

| 1st occurrence | Grade 1                                                          | Grade 2                                                                                                                             | Grade 3                                                                                                                                                                             | Grade 4                                                                                                                         |
|----------------|------------------------------------------------------------------|-------------------------------------------------------------------------------------------------------------------------------------|-------------------------------------------------------------------------------------------------------------------------------------------------------------------------------------|---------------------------------------------------------------------------------------------------------------------------------|
|                | Symptomatic Rx. Consider interruption of one or both trial drugs | Symptomatic Rx. Interrupt trial drugs, redose at same dose                                                                          | Symptomatic Rx. Interrupt trial drugs, redose 1 step lower                                                                                                                          | Symptomatic Rx. Interrupt trial drugs, redose 2 or more steps lower                                                             |
| 2nd occurrence | Grade 1                                                          | Grade 2                                                                                                                             | Grade 3                                                                                                                                                                             | Grade 4                                                                                                                         |

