|                | Symptomatic Rx. Consider interruption of one or both trial drugs | Symptomatic Rx. Interrupt trial drugs.
If previously:
a) grade 1 redose at same dose
b) $\geq$ grade 2 redose 1 step lower | Symptomatic Rx. Interrupt trial drugs.
If previously:
a) grade 1 redose 1 step lower
b) grade 2 redose 1 step lower
c) grade 3 redose at 1 or more steps lower          | Symptomatic Rx. Interrupt trial drugs.
If previously:
a) grade 1,2 redose 2 or more steps lower
b) grade 3,4 off study |
| 3rd occurrence | Grade 1                                                          | Grade 2                                                                                                                             | Grade 3                                                                                                                                                                             | Grade 4                                                                                                                         |
|                | Symptomatic Rx. Consider interruption of one or both trial drugs | Symptomatic Rx. Interrupt trial drugs.
If previously:
a) grade 1 redose at same dose
b) $\geq$ grade 2 redose 1 step lower | Symptomatic Rx. Interrupt trial drugs.
If previously:
a) grade 1 redose 1 step lower
b) grade 2 redose 1 or more steps lower
c) grade 3 redose at 1 or more steps lower | Symptomatic Rx. Interrupt trial drugs.
If previously:
a) grade 1,2 redose 2 or more steps lower
b) grade 3,4 off study |

**Figure 1. Stepwise dose reductions to cediranib and gefitinib for diarrhoea**[figure not shown]

The cediranib should be re-introduced first and dose modifications made to find a tolerable dose before the gefitinib is re-introduced.

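### Sections 7.4.3.1, 7.4.3.2, 7.4.3.4 and Table 10 disagree on interrupting trial drugs for persistent grade 1 diarrhoea, give no restart rule for it, and leave a gap in Table 10

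*Protocol*

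**What the plan says.** The Protocol deals with diarrhoea in several places.

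- **7.4.3.1** lists when patients should seek advice early. One trigger is "Grade 1 or 2 diarrhoea persists for over 24hrs despite treatment with loperamide". The others are grade 3, and any grade with vomiting, marked distension or inability to drink.
- **7.4.3.2** is headed "Management of persistent (>24h) or uncontrolled severe diarrhoea despite loperamide". Its first instruction is "Patients should be advised to stop the cediranib and gefitinib study tablets and care should be taken to prevent dehydration". It gives no grade for persistent diarrhoea and no restart condition.
- **7.4.3.4, text**, on grade 1: "Diarrhoea which is Grade 1 in severity can be managed symptomatically without necessitating interruption of the trial drugs". Duration makes no difference. Diarrhoea of grade 2 or above "in severity will require the trial drugs to be interrupted and restarted when the diarrhoea resolves to Grade 1 or less", with no time condition.
- **Table 10** says for grade 1, at every occurrence, "Consider interruption of one or both trial drugs". For grade 2 it interrupts the trial drugs. In the grade 3 column, the second and third occurrences list earlier grades 1, 2 and 3, ending at "c) grade 3 redose at 1 or more steps lower".
- **7.4.1** interrupts cediranib for toxicity of grade 3 or more. Its exceptions are proteinuria, hypothyroidism, hypertension and reversible posterior leukoencephalopathy syndrome. **7.4.2** has the matching rule for gefitinib and does list diarrhoea as an exception.

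After Table 10, the Protocol has cediranib re-introduced and its dose settled before gefitinib returns. Section 7.1 limits pauses to 14 days, or 21 in consultation with the Chief Investigator.

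**The concern.** Section 7.4.3 says both drugs are associated with diarrhoea, and 7.4.3.1 has patients told that they are likely to get it, so these rules will be used often. If the sections point in different directions, two sites can follow the Protocol faithfully and treat the same event differently, one taking both drugs away and the other continuing them.

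Two things are at stake. The first is patient care: a site looking for the rule should find one answer, and a patient who has been stopped should have a defined route back. The second is exposure. Gefitinib or its placebo is the only randomised component, and because cediranib returns first, each joint stop tends to last longest for that component. Differences between sites in how often drugs are stopped would then add variation in exposure that has no clinical cause.

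**Working it through.** No arithmetic applies. The check sets the instructions side by side by grade and duration.

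| Event | 7.4.3.1 and 7.4.3.2 | 7.4.3.4 text | Table 10, first occurrence | Result |
|---|---|---|---|---|
| Grade 1, up to 24 h | No stop instruction | Interruption not needed | Optional, one or both drugs | Compatible |
| Grade 1, over 24 h despite loperamide | Seek advice, then stop both | Interruption not needed | Optional, one or both drugs | **Conflict** |
| Grade 2, up to 24 h, no complicating symptoms | No prompt to seek advice | Interrupt | Interrupt | **Timing mismatch** |
| Grade 2, over 24 h despite loperamide | Seek advice, then stop both | Interrupt | Interrupt | Consistent |

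**Does 7.4.3.2 reach grade 1?** Its heading could be read with the word severe governing both terms, which would exclude low grades. Two features make that the weaker reading. Section 7.4.3.1 attaches the same 24-hour, despite-loperamide condition to grades 1 and 2 by name. And the next heading, 7.4.3.3, covers diarrhoea persisting over 48 hours without the word severe, so persistence is treated as a category of its own. On the narrow reading, a grade 1 or 2 patient told to call at 24 hours would reach no management section on persistence until 48 hours.

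**Restart after a stop at grade 1.** The threshold in 7.4.3.4 belongs to the sentence on grade 2 and above. Section 7.4.3.2 gives no threshold, and Table 10's grade 1 cells carry no redosing instruction. So within 7.4.3 the restart condition for this patient is undefined. Borrowing the grade 2 threshold does not help, because the patient was already at grade 1 when stopped.

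**Grade 2.** The 7.4.3.4 text and Table 10 require interruption as soon as grade 2 is present. A patient at home with uncomplicated grade 2 is not told to seek advice until 24 hours have passed despite loperamide, so the site may not know in time to apply its own rule.

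**Section 7.4.1.** Read alone, it interrupts cediranib at grade 3, while 7.4.3.4 interrupts both drugs at grade 2. Section 7.4.2 avoids this clash for gefitinib by exempting diarrhoea. Section 7.4.1 does not, and it even names diarrhoea as an example of a low-grade event for which a short cediranib break may help.

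**Table 10, grade 3 after grade 4.** The case can arise: a first grade 4 episode is followed by redosing two or more steps lower, so the patient may stay on treatment and later have grade 3. The grade 2 column covers an earlier grade 4 (grade 2 or above), and so does the grade 4 column (grades 3 and 4 together). Only the grade 3 column stops at an earlier grade 3, at both the second and the third occurrence.

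**The case against.** The best defence is a staged reading: 7.4.3.1 is home care, 7.4.3.2 and 7.4.3.3 cover failure of loperamide at 24 and 48 hours, and 7.4.3.4 sets doses by grade. On this view symptomatic management of grade 1 is the default, and 7.4.3.2 takes over once it has failed. The texts are also framed as guidance and recommendations, which leaves room for judgement, and a specific section would normally override the general rule in 7.4.1. This reading is coherent, but the Protocol does not state it: 7.4.3.4 makes no exception for duration and Table 10 keeps interruption optional for grade 1. A site cannot tell which was meant.

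Several stronger readings are tempting and should be set aside.

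- A reader might infer three incompatible instructions for grades 1 and 2 alike. The 7.4.3.4 text and Table 10 are both permissive for grade 1 and compatible with each other, and all of 7.4.3 agrees on grade 2 beyond 24 hours.
- A reader might infer that a patient stopped at grade 1 already meets the restart rule. That rule is written for grade 2 or higher. For grade 1 it is undefined, not satisfied.
- A reader might infer that 7.4.3.1 and 7.4.3.2 tell patients with grade 2 to keep dosing for 24 hours. They do not. They only give no earlier prompt to call.

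Sections 7.4.1 and 7.4.2 also allow restart on resolution after a short break for patients with multiple low-grade events. That could be borrowed for grade 1 diarrhoea, but it is written for several events together, and the 7.4.2 plan excludes diarrhoea.

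The Table 10 gap is narrow. Figure 1 was not visible in the copy read. The text describes it as ordering reductions by current dose, so it may bear on the gap.

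**Conclusion.** The point holds as an internal inconsistency in the Protocol. For grade 1 diarrhoea over 24 hours despite loperamide, one text stops both drugs and two leave them running or make interruption optional, and 7.4.3 has no workable restart criterion for a patient so stopped. Grade 2 has a timing mismatch, 7.4.1 lacks the exemption that 7.4.2 has, and Table 10 misses one reachable case. The first conclusion rests on the more natural reading of the 7.4.3.2 heading. On the narrower reading the heading is still ambiguous about whether both trial drugs are stopped.

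The size of the effect on exposure is unknown. The Protocol gives no diarrhoea incidence by arm, grade or duration, so any count of affected patients or lost treatment days would be guesswork.

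A reader might infer a biased progression-free survival comparison. The documents do not support that. Allocation is 1:1 (6.1), treatment is double-blind (7.6.1) and the primary population is intention-to-treat (16.2), so whatever reading a site adopts applies to both of its arms. Some dilution of the treatment contrast is possible but not shown. This should be corrected for patient care and consistent conduct. It does not threaten the validity of the primary analysis.

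**What to change.** Reconcile 7.4.3.1, 7.4.3.2, the text of 7.4.3.4, Table 10 and the exception list in 7.4.1 so that:

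- each combination of grade and duration has one instruction on interruption, with the grades covered by 7.4.3.2 stated;
- every stop has a restart condition that cannot already hold at the moment of stopping;
- the prompts for patients to seek advice match the point at which the site is expected to act;
- 7.4.1 says whether diarrhoea is governed there or in 7.4.3;
- the grade 3 column of Table 10 has a line for a previous grade 4 episode at the second and third occurrence.

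Which rule applies in each case is for the clinical team. The cost is wording in 7.4.3, one table and one exception list, plus a memo to sites. No extra patients, visits or procedures are needed.
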